## Method

### Design

The study concerns a multicenter RCT with 3 treatment arms with unequal sizes GST (planned *n*=162), individual ST (IST, planned *n*=108), and TAU (planned *n*=108). Ten treatment sites in the Netherlands participate in this trial: Emergis, GGZ Oost-Brabant Helmond, Oss and Boxmeer, IPGGZ Veendam and Groningen, PsyQ Amsterdam, Rotterdam, Zaandam, and Utrecht (see Appendix B for organisational structure). This study has been approved by the psychology department’s Ethics Committee of the University of Amsterdam. This trial is registered at the Netherlands Trial Register; NL9209 and complies with the World Health Organization Trial Registration Data Set. Requests for modifications to the study protocol (e.g., adding questionnaires, altering study procedures) will be formally submitted to the Ethics Committee of the University of Amsterdam for approval.

### Recruitment

Participants are recruited from the regular influx of patients at the participating sites. Patients will be informed about study purposes and invited to participate in this study when diagnosed with Cluster-C PD or when Cluster-C PD is presumed. Informed consent (see Appendix A) will be obtained by a research assistant or clinician before the start of the baseline measurements. We strive for diversity and high representativeness in the sample by recruiting from the regular instream of patients, minimal in/exclusion criteria, and verifying that participants are not excluded for other reasons than listed in the exclusion criteria. Figure 1 provides a schematic overview of the patient flow starting with recruitment.

**Fig. 1 Fig1:**
[figure not shown]
Flow chart of the study design

To ensure an adequate influx of participants in order to obtain the intended sample sizes, site-coordinators regularly update the central research team on the status of (and potential problems with) inclusion. Meetings are scheduled with sites facing inclusion problems so that tailored solutions can be implemented. Additional actions that are being undertaken to boost inclusion: recruiting a potential 11^th^ treatment site; recruiting more than the intended 42 patients at sites where inclusion fares well; increasing awareness of the study among prospective patients and referring clinicians by a website; organising a webinar aimed at educating referring general practitioners and clinicians on how to recognize Cluster-C PD and where to refer them.

### Patients

A total of 378 individuals with a primary Cluster-C PD diagnosis are planned to be recruited for this study. All diagnoses are determined by well-trained clinicians working in a multidisciplinary team. Inclusion criteria consist of (1) having received a primary diagnosis of APD, DPD, or OCPD based on the SCID-5-P [26]; F(2) being at least 18 years of age; (3) having sufficient Dutch language skills to participate in assessments and treatment; (4) being available and motivated to attend therapy for a period of one year regardless of offered treatment type (GST, IST or TAU). Additionally, participants are informed that they are not allowed to follow other psychological treatments in parallel to treatment received within the context of the study. Individuals are not eligible to participate if there is acute suicidality as determined by a clinician, or if they received a form of schema therapy in the last year.

### Sample size

Sample size calculations were based on symptom reduction effect sizes demonstrated in previous research on GST, TAU, and IST. In our pilot study, a 1-year pre-post effect size of d = 1.24 was found for GST on the primary outcome (severity of the primary PD). There is no data yet of TAU on this index. However, Bamelis and colleagues [12] found a difference between ST and TAU in recovery from PD-diagnosis of OR = 4.073 (81% (ST) vs 52% (TAU)). This is equivalent to an effect size d = .77. Secondly, in a recent multicenter trial, a difference between GST and TAU in reduction of BPD-severity of d = .73 was found [27]. Thirdly, the Svartberg et al. [28] RCT found a 1-year pre-post effect size of psychodynamic treatment, which is one of our TAU treatments, of d = .73 on an index of PD-severity. Taken together, it seems reasonable to assume a (large) pre-post effect size of TAU on PD-severity of d = .8, and also to assume a difference of d = .44 (1.24 – .8) between GST and TAU. Also note that this is a smaller effect size than found between ST and TAU in the Bamelis RCT [12] and between GST and TAU as treatments for Borderline PD [27].

The power analysis is based on 9 sites, despite 10 sites intent to participate, because sites might withdraw or not reach the intended N. For feasibility purposes a larger N is intended for the GST condition, as more participants can be treated at the same time in a group. With minimal N’s of 162 (GST), 108 (IST) and 108 (TAU) power of pairwise comparisons GST-IST and GST-TAU is 90% at an adjusted p-level of .025 to detect an effect size of d = .44 at post-test (or follow-up). For the GST-IST comparison, we don’t have expectations about the direction of a possible difference, but the power is sufficient to detect a medium effect size. One potential issue is treatment dropout. For pairwise comparisons of GST with the other two arms power is 80% to detect an RR = 2.5 at adjusted p = .025, for instance when dropout is 25% from GST vs. 10% from IST). (G)LMM analysis for repeated measures will be used to account for correlations introduced due to grouping (at multiple levels) and compensate for potential loss of power due to treatment drop-out. This type of analysis usually has greater power compared to non-multilevel/non-repeated measures analyses, however an actual power calculation for multilevel analysis with repeated measures and multiple sites is very difficult if not impossible because of the many random effects of the to-be-estimated model.

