### Randomization

Randomization of the participants is conducted by an independent researcher after completion of the baseline assessment. Computerized covariate adaptive randomization is used, considering the primary diagnosis and gender. Six cohorts per site are planned, randomized approximately every 10 working weeks. It is possible that sites where inclusion runs smoothly will end up doing more cohorts relative to sites where inclusion falls behind. To guarantee balanced conditions over time, the aim is to randomize cohorts of 7 participants at a time per site resulting in GST (n=3), IST (n=2) and TAU (n=2). As participant influx may vary from time to time, occasionally less or more than 7 participants may be randomized. The distribution over the 3 conditions then will depend on 1) the capacity at the site in question, or 2) the need to allocate more participants to 1 particular condition in order to maintain the overall 3:2:2 distribution. At least 3 participants will be randomized per cohort as to ensure a chance for each participant to end up in one of the 3 conditions. The assigned intervention will be revealed to the patient in the first treatment session by the therapists.

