##### Analyses

All analyses are planned to be carried out by SPSS or R statistical software and Excel (for Bootstraps).

Primary and secondary outcomes are analysed with Linear Mixed Models (LMM), with random effect of site. As data of group members are not independent because group members might influence each other, this dependency needs to be taken into account. With the semi-closed group format, groups change in composition every 10 sessions, and participants will share different amounts of time in sessions with group peers: from all group sessions to 10 group sessions. It is plausible to model covariances as a function of the amount of time (i.e., sessions) patients have spent together in a group. This can be achieved in a multilevel model with repeated measures by specifying a Toeplitz covariance structure to model this dependency on the group level. In case this Toeplitz structure turns out to be unsuitable to model the dependency, another (less complex) structure will be specified. For the repeated part at the individual level, the best fitting covariance structure will be chosen (e.g., AR1, ARMA11, Unstructured). If residuals deviate substantially from normal distribution, Generalized LMM (GLMM) will be used with an appropriate distribution (e.g., negative binomial or gamma in case of skewed distributions). All analyses are conducted on the basis of intention-to-treat and will be controlled for initial symptom severity. Dropout from treatment will be analysed with GLMM survival analysis with site as random effect. To take into account participants’ potential influence on each other in group treatment, again a Toeplitz covariance structure will be specified to model this dependency unless a different structure turns out to be more suitable. The three arms will be mutually compared, with a primary interest in the GST-TAU and the GST-IST comparisons. Although the IST-TAU difference is not part of the main research questions, this difference will be analysed exploratively. Tests of predictors and moderators (sleep quality, introversion, autism traits, childhood trauma, verbal intelligence, demographic characteristics) will be done by similar (G)LMM analyses, with the predictor, predictor x time, predictor x treatment, and predictor x time x treatment interactions added to the model.

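### The fixed .025 level for each of GST-TAU and GST-IST is valid, but Holm's step-down would give more power at the same 5% family-wise error and the same N (optional improvement)

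*Protocol article*

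**What the plan says.** The Sample size section gives minimum arm sizes of 162 (GST), 108 (IST) and 108 (TAU) and states 90% power for each of GST-IST and GST-TAU "at an adjusted p-level of .025 to detect an effect size of d = .44", at post-test or follow-up. The same adjusted level is used again in that section for the treatment-dropout comparison.

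The Analyses section says: "The three arms will be mutually compared, with a primary interest in the GST-TAU and the GST-IST comparisons". IST-TAU is left exploratory. That section gives no significance level and names no multiplicity procedure.

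Nowhere does the article say that the level freed by one significant result passes to the other test. It does not rank the two clinical comparisons either. The Cost-Effectiveness and Cost-Utility Analyses section calls GST-TAU primary and GST-IST secondary, but only for the economic evaluation.

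**The concern.** Two comparisons share the primary interest and each is held at .025, which is .05/2. A single-step split keeps the second test at .025 even after the first has succeeded. Holm's procedure releases the full .05 to the second test in that case, with the same 5% bound on the chance of any false claim. Because it orders the tests by the observed p-values, nobody has to decide in advance whether GST-TAU or GST-IST comes first.

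What is at stake is mainly power for GST-IST. The d = .44 was derived for GST versus TAU only (1.24 − .8 in the Sample size section). For GST-IST the authors say they do not "have expectations about the direction of a possible difference", and the section headed This study hypothesises only that GST does not do worse than IST. A GST-IST difference smaller than .44 is therefore plausible, and there the planned test is well short of 90% power.

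**Working it through.** **Inputs.** From the Sample size section: arms 162, 108 and 108; d = .44 with SD 1; level .025; stated power 90%. The Randomization section confirms the ratio ("maintain the overall 3:2:2 distribution"). Sidedness is not stated and is taken as two-sided, because no direction is expected for GST-IST and because only two-sided .025 reproduces 90%.

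**Step 1: reproduce the stated power.**
- Standard error of a contrast: √(1/162 + 1/108) = √0.01543 = 0.1242.
- Noncentrality: .44 / 0.1242 = 3.54.
- Critical value at two-sided .025: 2.241.
- Power: Φ(3.54 − 2.241) = Φ(1.30) = 90.3%. With the noncentral t on 268 df it is 90.0%.
- One-sided .025 or two-sided .05 would give 94.3%, and one-sided .05 would give 97.1%, so neither alternative matches.

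The stated 90% is right.

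**Step 2: correlation of the two tests.** Both contrasts use the GST arm, so ρ = (1/162) / (1/162 + 1/108) = 0.00617 / 0.01543 = .40.

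**Step 3: the two rules.**
- Fixed split: reject a comparison if |z| > 2.241.
- Holm: reject it if |z| > 2.241, or if |z| > 1.960 and the other comparison has |z| > 2.241.

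The second rule contains the first, so Holm never rejects less.

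Error control follows directly. If both nulls are true, a false rejection needs the smaller p to be at most .025, which has probability at most 2 × .025 = .05. If only one null is true, a false rejection needs that p to be at most .05.

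**Step 4: size of the gain.** Results from 2,000,000 draws of bivariate normal z-statistics with ρ = .40, two-sided. The Monte Carlo standard error is about 0.02 points at 90%: √(.9 × .1 / 2,000,000) = 0.0002. Each cell shows fixed split → Holm, in %.

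| True d: GST-TAU, GST-IST | GST-TAU rejected | GST-IST rejected | Both rejected | At least one (both rules) |
|---|---|---|---|---|
| .44, .44 | 90.4 → 93.5 | 90.3 → 93.5 | 83.2 → 89.5 | 97.5 |
| .44, .30 | 90.4 → 91.7 | 57.0 → 66.6 | 54.2 → 65.2 | 93.1 |
| .44, .20 | 90.4 → 90.8 | 26.4 → 35.9 | 25.7 → 35.5 | 91.1 |
| .44, −.20 | 90.4 → 92.3 | 26.3 → 35.2 | 21.2 → 31.9 | 95.5 |
| .44, 0 | 90.4 → 90.5 | 2.5 → 4.6 (error) | 2.0 → 4.3 | 90.9 |
| 0, 0 | 2.5 → 2.7 (error) | 2.5 → 2.7 (error) | 0.2 → 0.6 | 4.8 (family-wise error) |

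The GST-IST values other than .44 are illustrations; the article gives no expected GST-IST effect. The −.20 row covers IST doing better than GST, since no direction is expected.

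**The case against.** **The article does not name a testing rule.** The .025 stands only in the power calculation, the word Bonferroni appears nowhere, and .025 is also Holm's first step. An analysis plan that is not shown could already use a step-down rule without contradicting the article. This stands as a limit. What can be said is that the one level the article states, applied as written to both tests, is an equal single-step split.

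**Nothing is wrong with the split.** It is simple, controls the 5% error and delivers the stated power. This stands in full. A reader might infer that the plan contains an error or that its sample size is unsound, and the documents support neither.

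**The gain depends on the scenario.** A reader might also infer that power is being given away on both main questions. That holds only if both differences are real. If GST and IST are equal, which fits the stated hypothesis, GST-TAU gains about 0.1 point and the chance of at least one rejection is unchanged. There is also a trade: when GST-TAU is real and GST-IST is null, the error on GST-IST rises from 2.5% to 4.6%, although this stays inside the 5% bound.

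**Intervals are simpler with a fixed .025.** A .025 test has a directly matching 97.5% interval, and for a does-not-do-worse hypothesis the interval is what readers need. Holm has no equally simple match. With raw p-values of .04 and .04, Holm rejects neither, yet both 95% intervals exclude zero. With .01 and .04, Holm rejects both, yet the second 97.5% interval includes zero. This is a real drawback, to be handled by labelling.

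**Conclusion.** The point holds as an optional, cheap improvement. At the planned N, Holm is at least as powerful as the fixed .025 level in every scenario and keeps family-wise error at or below 5%. The gain is about 3 points per comparison and 6 points for winning both if both effects are .44. It is about 9 to 10 points for GST-IST if that effect is .20 to .30 and GST-TAU is .44. It is close to nil for GST-TAU if GST and IST do not differ.

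The figures assume two-sided tests, equal variances, independent observations and the planned arm sizes, with one outcome at one time point. They ignore clustering by therapy group and site, as the article's own calculation does, so they show the relative gain and not the power of the planned mixed model. Neither rule covers a choice between post-test and follow-up, which the Sample size section leaves open.

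**What to change.** Add one sentence to the Analyses section before outcome data are analysed: the GST-TAU and GST-IST tests of the primary outcome, at one named time point, are judged by Holm's step-down at family-wise .05. Keep .025 in the Sample size section as the conservative planning level; N does not change.

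Report Holm-adjusted p-values: 2 × p for the smaller, and the larger of that value and the other raw p for the second. Give with them either 97.5% (Bonferroni) intervals, or 95% intervals labelled as unadjusted and not used for the decision.

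The cost is that sentence, plus a note that the intervals do not correspond exactly to the Holm decisions. No change to recruitment, visits or conduct is needed. If the sponsor values exactly matching intervals more than the extra power, keeping the fixed .025 is defensible; the Analyses section should then state that level.

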### Randomization

Randomization of the participants is conducted by an independent researcher after completion of the baseline assessment. Computerized covariate adaptive randomization is used, considering the primary diagnosis and gender. Six cohorts per site are planned, randomized approximately every 10 working weeks. It is possible that sites where inclusion runs smoothly will end up doing more cohorts relative to sites where inclusion falls behind. To guarantee balanced conditions over time, the aim is to randomize cohorts of 7 participants at a time per site resulting in GST (n=3), IST (n=2) and TAU (n=2). As participant influx may vary from time to time, occasionally less or more than 7 participants may be randomized. The distribution over the 3 conditions then will depend on 1) the capacity at the site in question, or 2) the need to allocate more participants to 1 particular condition in order to maintain the overall 3:2:2 distribution. At least 3 participants will be randomized per cohort as to ensure a chance for each participant to end up in one of the 3 conditions. The assigned intervention will be revealed to the patient in the first treatment session by the therapists.

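### In cohorts that are not exactly 7, the arm split follows site capacity or catch-up, and the stated model does not compare arms within cohort

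*Protocol article*

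**What the plan says.** All of the allocation text is in the Protocol article, section Randomization.

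- Normal case: "the aim is to randomize cohorts of 7 participants at a time per site resulting in GST (n=3), IST (n=2) and TAU (n=2"). The stated purpose is balance between the conditions over time. Six cohorts per site are planned, about 10 working weeks apart.
- Exception: "occasionally less or more than 7 participants may be randomized".
- First rule for the split in the exception: "The distribution over the 3 conditions then will depend on 1) the capacity at the site in question".
- Second rule, given as an alternative to the first and with no order of precedence: "the need to allocate more participants to 1 particular condition in order to maintain the overall 3:2:2 distribution".
- Safeguards: "Randomization of the participants is conducted by an independent researcher after completion of the baseline assessment". A minimum cohort size is meant to keep every arm possible: "At least 3 participants will be randomized per cohort as to ensure a chance for each participant to end up in one of the 3".
- Method: "Computerized covariate adaptive randomization is used, considering the primary diagnosis and gender". Site, cohort and time are not among the listed factors.

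The Analyses section states: "Primary and secondary outcomes are analysed with Linear Mixed Models (LMM), with random effect of site". It adds a covariance structure for patients who share group sessions, control for initial symptom severity, and analysis by intention to treat. It names no term for cohort or calendar time.

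**The concern.** While every cohort is 3:2:2, each patient has the same chance of GST whichever cohort he or she joins, so arm and cohort are unrelated. Once the split depends on capacity or catch-up, that chance varies between cohorts of one site. GST patients then come disproportionately from GST-heavy cohorts and TAU or IST patients from the others.

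If those cohorts also differ in prognosis, the difference enters both primary contrasts. Possible reasons are a changing referral mix, growing therapist experience, or choices about which patient joins which cohort. A site effect cannot remove a difference between cohorts of the same site. Baseline severity removes only the part of prognosis that it carries. The group-level covariance describes dependence among patients who sat in the same group; it does not make the comparison between arms a within-cohort one.

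Capacity is also unlikely to be neutral between arms. Under Group schema therapy, places open in a cycle, usually three every 10 sessions. The section on drop-out and deviation from the treatment protocol describes schema-therapist capacity at the sites as limited.

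**Working it through.** **1. The plan's own figures.** 9 sites × 6 cohorts × 7 patients = 378. The 54 cohorts give 54 × 3 = 162 for GST and 54 × 2 = 108 each for IST and TAU, as stated. With 162 against 108, d = .44 and two-sided alpha .025, power is 0.903 (normal approximation) or 0.900 (noncentral t), matching the stated 90%. These totals assume 3:2:2 throughout.

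**2. How far the arm probability can move.** The GST share is 3/7 = 43% in a cohort of 7. The off-size rule permits, for example:

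- 1:1:1, 1/3 = 33%
- 2:2:1, 2/5 = 40%
- 3:1:1, 3/5 = 60%
- 4:1:1, 4/6 = 67%
- 1:2:2, 1/5 = 20%

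The share can rise, fall or hardly change.

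**3. Illustrative bias.** Assumptions that are not in the article:

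- A fraction f of cohorts is off-size, half of them 3:1:1 and half 1:2:2.
- Mean prognosis is +δ/2 in the former, −δ/2 in the latter and 0 in cohorts of 7.

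Per cohort:

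- Expected GST count: 3(1−f) + 3f/2 + f/2 = 3 − f. Prognosis sum: (f/2)(3 − 1)(δ/2) = fδ/2.
- Expected TAU count: 2(1−f) + f/2 + f = 2 − f/2. Prognosis sum: (f/2)(1 − 2)(δ/2) = −fδ/4.
- Bias = GST mean − TAU mean = δ × (f/2) × [1/(3−f) + 1/(4−f)].

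IST has the same counts as TAU here, so GST-IST has the same bias.

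| f | multiplier of δ | δ = 0.3 SD | δ = 0.5 SD |
|---|---|---|---|
| 10% | 0.030 | 0.009 | 0.015 |
| 20% | 0.062 | 0.019 | 0.031 |
| 50% | 0.171 | 0.051 | 0.086 |

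Relative to d = .44 this is 2% to 7% for f = 10% to 20%, and 12% to 19% for f = 50%.

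**4. Simulation with more extreme splits.** 54 cohorts, 1,200 runs per setting, true effect zero, two-sided alpha .025, GST against TAU. Off-size cohorts had 4 to 10 patients, with GST given either all but two places or only one. The SD of cohort means was 0.2 to 0.4 patient SD.

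- Split unrelated to prognosis: bias below 0.01 SD, type I error about .02 to .04.
- Correlation 0.5 to 1 between split and prognosis, unadjusted: bias 0.02 to 0.10 SD and type I error about .03 to .05 at f = 20%; bias 0.07 to 0.24 SD and type I error about .05 to .34 at f = 50%.
- Comparison within cohort: bias below 0.01 SD and type I error about .02 to .04 in every setting. The SD of the estimate rose by at most 0.004 at f = 20% (for example 0.121 to 0.125) and by 0.002 to 0.013 at f = 50%.

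**The case against.** The safeguards are real. An independent researcher allocates a whole cohort by computer after baseline, with at least three patients so that all arms stay possible. Cohorts of 7 are unaffected, and off-size cohorts are described as occasional. The article is condensed, so a full protocol or SAP may say who sets the off-size split and may list further random effects. Sample size does mention grouping at multiple levels. This limits the size of the problem. It does not remove it, because the article states the capacity and catch-up rule outright and the model it describes contains no within-cohort comparison.

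Four stronger readings are tempting but not supported:

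- *Recruiting staff can foresee a patient's arm.* Staff plausibly know their own open places, and Assessments lets a non-blind research assistant perform assessments before randomization. But nothing says that staff know the coming split or the running totals. Such knowledge could affect which cohort a patient joins, not the arm within it.
- *A GST-poor cohort has to be followed by a GST-rich one.* Catch-up is one of two alternatives, applies only to off-size cohorts, and refers to the overall ratio, not to the next cohort at that site.
- *The model adjusts for nothing but site.* It also has the group-level covariance and control for initial severity.
- *The bias is a large part of the design effect.* If every cohort were off-size, step 3 would give 0.417δ, or 0.125 to 0.208 SD. That does not fit a rule described as occasional.

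**Conclusion.** The point holds as a correctable weakness of design and analysis; it does not show that the primary contrasts are biased. In off-size cohorts the arm probability differs between cohorts of the same site, and the stated balancing factors and model do not account for this. Bias arises only if prognosis or calendar drift tracks the split.

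Its size cannot be derived from the article, which gives neither the share of off-size cohorts nor their splits. On the assumptions of step 3 it is about 0.01 to 0.03 SD at 10% to 20% off-size and 0.05 to 0.09 SD at half. It would be larger with more extreme splits and about zero if split and prognosis are unrelated. The change is worth making because it is cheap and amounts to analysing the trial by the batches in which it already randomises.

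**What to change.** 1. **Allocation.** Replace the capacity and catch-up sentence. For a cohort of any size other than 7, the independent researcher sets the arm counts by a pre-specified central rule targeting 3:2:2, either a fixed table by cohort size or random rounding. The rule is concealed from recruiting staff and applied only after the site has closed the cohort's patient list. Covariate-adaptive allocation on diagnosis and gender continues within those counts. Capacity may limit the size of a cohort, not its ratio.

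2. **Analysis.** In the primary LMM, compare arms within randomisation cohort, with cohort within site as fixed effects or an equivalent within-cohort contrast. A random cohort intercept removes the confounding only in part. This is needed even with a fixed table, since rounding still moves the ratio (1:1:1 in a cohort of 3 gives GST 33%, against 43% in a cohort of 7).

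**Cost.** Roughly 54 cohort parameters (9 × 6) with a small loss of precision, an occasional smaller cohort when an arm is full, and a final ratio that may miss 3:2:2 by a few patients.
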